#### Primary and Secondary Analyses

All data analyses will be based on the intention-to-treat principle [53]. Continuous outcomes (eg, measures of perinatal distress, quality of life, couple relationship satisfaction) will be analyzed using general linear mixed models, and multilevel modelling will be used for nested data, to deal with any missing data.

#### Cost-Effectiveness Analysis

The evaluation will examine the perspectives of costs to health services and to society. Unit costs will be applied to resource-use data collected on health care (primary care and hospital data), work time/productivity, and intervention establishment/delivery. The AQol-8D [56], a multi-attribute utility instrument, will be used and scored using the Australian algorithm [58]. Resultant utility weights will be multiplied by duration to estimate quality-adjusted life years. Incremental cost-utility ratios will be estimated as the primary outcome factor of the economic evaluation. An alongside-trial analysis will be undertaken. Sensitivity analyses will be used to identify key factors driving the results and bootstrapped standard errors will be used to estimate the 95% confidence interval for the incremental cost-effectiveness ratio.

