#### Inclusion Criteria

Participants will be included in the trial if they are a co-parenting male-female couple aged 18 years or older, this is the first child for both parents, gestation is between 26 and 38 weeks at registration (couples registering before 26 weeks of gestation will be reminded by email to retake the screening survey when they reach the 26-week time point), and the pregnancy involves a single child. Participants must also be literate in English, have Internet and mobile phone access, and complete the baseline assessment. Both parents must be eligible for the couple to participate. Exclusion criteria are presented in Figure 1.

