#### Follow-Up Assessments

Follow-up assessments will be at 13 and 26 weeks post-baseline. For the purposes of these assessments, couples will be treated as individual participants and emailed an individualized online survey link. To maximize retention, participants will be reminded to complete the survey via scheduled emails. If the participant has not responded within two weeks of the due date, a researcher (blind to treatment allocation) will phone the participant, establish ongoing consent from the participant, and attempt to obtain the assessment over the phone. Participants will be offered an AUD $20 gift voucher (AUD $40 per couple) for completing each follow-up assessment.

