#### Sample Size

A total of 240 couples (120 couples per group) will be recruited. A sample size of 240 will give a power of .80 for detecting a significant *Time* x *Condition interaction* (*P*<.05) over three occasions of measurement, with a small effect size of f=0.082 [50,51].

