#### Descriptive Analyses

Baseline data from the two program groups will be compared to check for comparability of the groups. Chi-square tests will be used for categorical variables, ANOVA tests for normally distributed continuous variables, and Kruskal-Wallis tests for non-parametric data. Any differences detected will be controlled for during the subsequent analyses.

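### Adjustment of the QALY difference for baseline AQol-8D utility should be fixed in advance, not left to a baseline test

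*Protocol article*

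**What the plan says.** All of this is in the protocol article.

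- **Utility and QALY** (Cost-Effectiveness Analysis). The AQol-8D is described as "a multi-attribute utility instrument, will be used and scored using the Australian algorithm", and then: "Resultant utility weights will be multiplied by duration to estimate quality-adjusted life years". No covariate is named for the QALY comparison.
- **Role of the QALY** (same section): "Incremental cost-utility ratios will be estimated as the primary outcome factor of the economic evaluation". Sensitivity analyses are planned without stated content, and bootstrapped standard errors give the confidence interval.
- **Baseline adjustment** (Descriptive Analyses, under the same Data Analyses heading and before the economic section): "Baseline data from the two program groups will be compared to check for comparability of the groups". The tests are chi-square, ANOVA or Kruskal-Wallis, and then: "Any differences detected will be controlled for during the subsequent analyses". The variables to be compared and the threshold for detection are not listed.
- **Timing** (Follow-Up Assessments): "Follow-up assessments will be at 13 and 26 weeks post-baseline". The Sample Size section counts three measurement occasions. The timing marks in Table 2 did not survive text extraction, so AQol-8D measurement at 0, 13 and 26 weeks is a reasonable inference and not something read from the table.

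**The concern.** The Descriptive Analyses rule decides on adjustment by testing for a baseline difference. Under randomisation any such difference is due to chance, so the test answers a question whose answer is already known. Adjustment is useful when the baseline variable predicts the outcome. Baseline utility can be expected to do so strongly: it is one of the values from which a 26-week QALY is built, and it is correlated with the other two.

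Two things are at stake. First, when the test is not significant, whatever imbalance exists passes into the incremental QALY, which is the denominator of the main economic ratio. Second, precision is given up although the value needed to recover it is, by reasonable inference, already collected. There is also a smaller point. If the covariate is chosen once in the observed data and the bootstrap holds that choice fixed, the interval does not reflect the selection step.

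**Working it through.** **The plan's own figures.** The article gives no utility, SD or QALY figure to reproduce. Its one design figure, power 0.80 for 240 at f=0.082 over three occasions, is reproduced as 0.799 if a correlation of 0.5 between occasions is assumed. It does not bear on this point.

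**Inputs from the article.** Two intervals of 13 weeks (0.25 year each); 120 couples per arm, hence 240 parents per arm.

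**Assumed inputs.** Equal utility SD at all three times; the same correlation r between any two times, 0.5 to 0.7; trapezoidal QALY; partner correlation 0.2 to 0.4; utility SD 0.15 to 0.20; a constant program effect of 0.35 SD at weeks 13 and 26.

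**Step 1: weights.** QALY = 0.125·u0 + 0.25·u13 + 0.125·u26.

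**Step 2: variance and covariance with baseline (utility SD = 1).**
- Variance = (0.125² + 0.25² + 0.125²) + 2r(0.125×0.25 + 0.125×0.125 + 0.25×0.125) = 0.09375 + 0.15625r.
- Covariance with u0 = 0.125 + 0.375r.
- Variance after adjustment = variance − covariance².

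| r | Variance | Covariance | Adjusted variance | Cut in variance | Cut in SE |
|---|---|---|---|---|---|
| 0.5 | 0.1719 | 0.3125 | 0.0742 | 57% | 34% |
| 0.6 | 0.1875 | 0.3500 | 0.0650 | 65% | 41% |
| 0.7 | 0.2031 | 0.3875 | 0.0530 | 74% | 49% |

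**Step 3: does this depend on the trapezoid?** Take r = 0.6. If each interval takes its end value, the variance is 0.125 + 0.125×0.6 = 0.20 and the covariance 0.5×0.6 = 0.30, so adjustment leaves 0.20 − 0.09 = 0.11, a 45% cut. If each takes its start value, the covariance is 0.25 + 0.25×0.6 = 0.40, leaving 0.20 − 0.16 = 0.04, an 80% cut. The gain is large under any of the three.

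**Step 4: what an unflagged imbalance does (r = 0.6, trapezoid).**
- SE of the baseline difference, all parents: SD × √(2(1 + partner correlation)/240) = 0.100 to 0.108 SD.
- Shift in the unadjusted QALY difference for a 1-SE imbalance: 0.35 × (0.100 to 0.108) = 0.035 to 0.038 SD, or 0.005 to 0.008 QALY.
- Assumed effect: 0.375 × 0.35 = 0.131 SD, or 0.020 to 0.026 QALY. The shift is 27% to 29% of it.
- A 1-SE imbalance has a two-sided p of about 0.32, so it would not be flagged. If detection means a 5% test (an assumption), imbalances up to 1.96 SE go unadjusted, which is about 52% to 56% of the assumed effect.

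**Step 5: one parent sex at a time.** With 120 per arm, SD 0.10 to 0.20 and r 0.3 to 0.7, the SE is SD × √(2/120) = 0.013 to 0.026. A 1-SE imbalance then shifts the QALY difference by (0.125 + 0.375r) × SE = 0.003 to 0.010.

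**The case against.** The strongest reply has four parts.

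1. *The article does provide for adjustment.* This stands. A reader might infer that the QALY will not be adjusted for baseline utility at all. That goes too far: the Descriptive Analyses rule promises control of detected differences in later analyses, and the cost-utility analysis is one of them. What can be criticised is that the adjustment is conditional on a test.

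2. *A condensed article may leave the QALY regression to a fuller plan.* This stands for what the article leaves unsaid, such as the interpolation rule. It does not cover the test-triggered rule, which the article states. That rule applies to every outcome, but it matters particularly here because baseline utility is part of the outcome itself.

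3. *Chance imbalance is ordinary sampling error.* This stands. The unadjusted difference is unbiased over repeated randomisations, and the bootstrap is meant to express that variation. The loss is precision, together with a shift conditional on the imbalance that occurred. Stratification on baseline EPDS may reduce the imbalance somewhat, although it splits couples into only two groups.

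4. *The sizes rest on assumed inputs.* This also stands, which is why they are given as ranges.

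A further tempting reading is that multiplying weights by duration commits the plan to a step function and leaves the incremental QALY uncertain up to two-fold. The wording does not support this, because a trapezoid is also a weight (the interval mean) times a duration. Nor is two-fold a bound. For a constant effect d, start-value, trapezoid and end-value rules give 0.25d, 0.375d and 0.50d. For an effect at week 13 only, all three give 0.25d. For an effect at week 26 only they give 0, 0.125d and 0.25d, so the ratio of the extremes has no limit. The trapezoid is itself an assumption, since it draws a straight line across a birth.

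**Conclusion.** The point holds as a free improvement. The article makes adjustment for baseline utility in its main economic analysis depend on a baseline test, and that is a poor basis for the choice. Under a trapezoidal QALY and a within-person correlation of 0.5 to 0.7, prespecified adjustment would cut the QALY variance by about 57% to 74% and the standard error by 34% to 49%. Under the further assumptions of Step 4, an imbalance of one standard error, too small to be flagged, moves the QALY difference by a little over a quarter of the assumed effect. None of the utility inputs comes from the article. The documents do not support calling the planned estimate biased, saying that adjustment is absent, or treating the QALY formula as wrong.

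**What to change.** - In Cost-Effectiveness Analysis, add: the between-arm QALY difference is estimated by regression adjusted for baseline AQol-8D utility, irrespective of any baseline comparison, and the same adjustment is made within each bootstrap replicate.
- In Descriptive Analyses, exempt this covariate from the rule that ties adjustment to detected differences.
- As a clarification only, name the QALY as the trapezoidal area under each parent's utility at 0, 13 and 26 weeks, if that is what is meant.

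The cost is a few words of analysis text. If the AQol-8D is collected at baseline, as inferred, no new data are needed. The change should be recorded before the outcome data are analysed.

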#### Randomization

Allocations will be generated by the Goji program, a web-based research trials management system developed at Queensland University of Technology, Australia, by the same web developers who programmed the *Baby Steps* programs. When the researcher notifies Goji that a participating couple has completed their baseline assessment, Goji will allocate the participants to a research group, randomizing couples as a unit. Randomizations will be in permuted blocks, and stratified by scores on the EPDS: neither parent distressed (father <5; mother <7) versus either parent distressed (father >5; mother >7). These cut-off scores represent optimum screening levels for depressive or anxiety disorders in fathers and mothers [7]. After randomization, a couple’s access to the allocated program will be granted by a researcher not blind to treatment allocation, and participants will be notified by email that they are able to log into the online program through their registered account.

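### The 95% interval for the ICER rests on bootstrapped standard errors, which have no stable value when the QALY difference may lie within a few standard errors of zero

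*Protocol article*

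**What the plan says.** The Cost-Effectiveness Analysis section of the protocol article names the outcome: "Incremental cost-utility ratios will be estimated as the primary outcome factor of the economic evaluation". It builds the denominator from AQoL-8D utilities: "Resultant utility weights will be multiplied by duration to estimate quality-adjusted life years". For precision it states that "bootstrapped standard errors will be used to estimate the 95% confidence interval for the incremental cost-effectiveness ratio".

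Cost-effectiveness is the second aim under Trial Aims and is also among the Hypotheses. Three other places bear on the size of the denominator:

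- Follow-Up Assessments: "Follow-up assessments will be at 13 and 26 weeks post-baseline". The QALY horizon is therefore half a year.
- Sample Size: "A total of 240 couples (120 couples per group) will be recruited", with power stated "over three occasions of measurement, with a small effect size of f=0.082".
- Well-Being Program – Experimental Condition: the experimental arm contains all the control content plus five further modules, so the comparator is active.

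Under Randomization, allocation is by "randomizing couples as a unit".

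**The concern.** The ICER is the cost difference divided by the QALY difference, and both are estimated with error. If the denominator has appreciable probability near zero, the ratio has no finite variance. The standard deviation of the bootstrap ratios is then set by the few replicates whose QALY difference falls closest to zero. An interval of the form ICER ± 1.96 × SE inherits that.

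The sign is a second problem. A negative ratio arises when the program is cheaper and better (dominant), and also when it is dearer and worse (dominated). An interval on the ratio scale puts these opposite results side by side.

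At stake is the main economic result. The planned interval may be so wide and so dependent on the random seed that it says little about the cost-effectiveness hypothesis.

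**Working it through.** **1. The plan's own figure.** The article gives no QALY difference, utility SD or cost SD. The nearest stated figure is the power: 0.80 for N = 240, three occasions, f = 0.082. For a repeated-measures interaction, λ = f² × N × m / (1 − ρ). With an assumed ρ = 0.5, λ = 0.006724 × 240 × 3 / 0.5 = 9.68 on 2 and 476 df, which gives power 0.799. The stated 0.80 is reproduced. (ρ = 0 gives 0.49 and ρ = 0.7 gives 0.96.)

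**2. What f = 0.082 implies for the QALY difference, if AQoL-8D utility showed exactly that effect.** In utility SD units, the final difference is d = 0.082 / √(pattern variance / 4).

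- Constant from week 13, pattern (0, 1, 1): variance 2/9, so d = 0.348.
- Linear, pattern (0, ½, 1): variance 1/6, so d = 0.402.

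The trapezoid weights for 0, 13 and 26 weeks are 0.125, 0.25 and 0.125 years. The QALY difference is 0.375 × 0.348 = 0.130, or 0.25 × 0.402 = 0.100 (0.125 × 0.402 at week 26 plus 0.25 × 0.201 at week 13).

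With ρ = 0.5 the QALY SD is √0.1719 = 0.415 unadjusted and √0.0742 = 0.272 adjusted for baseline utility. With 120 units per arm, multiply by √(2/120) = 0.129 to get SEs of 0.0535 and 0.0352. The distance from zero, z = difference / SE, is:

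| Pattern | z unadjusted | z baseline-adjusted |
|---|---|---|
| Constant from week 13 | 2.44 | 3.71 |
| Linear | 1.88 | 2.86 |

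The chance that the estimated QALY difference is zero or negative is 0.7% and 3.0% unadjusted, and 0.01% and 0.2% adjusted.

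**3. Behaviour of the planned interval.** Simulation assumptions: 120 units per arm, normal QALYs, lognormal costs independent of QALYs, cost difference 0.15 SD, 600 trials, 1,000 bootstrap draws each. For scale, the first-order (delta-method) SE divided by the ICER is √(1/z_C² + 1/z²), with z_C = 0.15/0.129 = 1.16.

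| z | Draws with QALY difference ≤ 0 | First-order SE / ICER | Bootstrap SE / true ICER, median (5th–95th percentile) | Coverage of ± 1.96 SE |
|---|---|---|---|---|
| 1.0 | 25% | 1.32 | 27 (1.3–381) | 98.3% |
| 2.0 | 8.1% | 1.00 | 17 (0.6–489) | 99.0% |
| 2.5 | 3.5% | 0.95 | 6.9 (0.6–174) | 99.3% |
| 3.5 | 0.7% | 0.91 | 1.35 (0.55–81) | 98.5% |
| 5.0 | 0.0% | 0.88 | 0.96 (0.57–2.2) | 98.5% |

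Over z from 0.5 to 5, Fieller limits covered 94.0–96.5% and bootstrap percentile limits for the ratio 94.5–98.5%.

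**4. More replicates do not help.** One fixed result was resampled with ten seeds, using a normal approximation to the bootstrap distribution. SE / ICER ranged as follows:

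| z | 1,000 draws | 10,000 draws | 100,000 draws |
|---|---|---|---|
| 2.44 | 2.9–99 | 13–200 | 27–119 |
| 3.0 | 1.4–9.8 | 2.0–35 | 8.2–27 |

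The lower end rises with the number of draws, as expected when the variance is not finite.

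**5. Illustration in money, all inputs assumed.** Utility SD 0.15, QALY SD 0.064, cost difference AUD 200, cost SD AUD 2,500, 120 per arm. At d = 0.35 the QALY difference is 0.375 × 0.35 × 0.15 = 0.0197. The SE is 0.064 × 0.129 = 0.0083, so z = 2.4, and the true ICER is 200 / 0.0197 ≈ AUD 10,000 per QALY. Three simulations with these inputs, one of them with lognormal costs, gave median interval widths of about AUD 0.41, 0.66 and 0.69 million. The 5th percentiles were AUD 41,000 to 47,000 and the 95th AUD 15.5 to 20 million, with coverage about 99–100%. At d = 0.2 the median width was about AUD 3 million. Net-benefit intervals from the same replicates covered about 94–96%.

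**The case against.** **Wording.** The clause may be loose language for bootstrap percentile limits, which behaved much better above. That is possible. But the text names standard errors, and percentile limits on a ratio keep the sign problem once draws cross zero, so the sentence needs correcting on either reading.

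**A reader might infer that a near-zero denominator is the expected case.** The article does not support this. It gives no expected QALY difference, and at the effect used for power the estimate would rarely be zero or negative (0.01–3%). The point needs less than that: the bootstrap SE is already unstable at z of 2 to 2.5, and its upper tail is still long at 3.5.

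**The inputs may be pessimistic.** Both parents are assessed. If they share the effect and their within-couple correlation is 0 to 0.5 (assumed), z rises by √(2/(1+ICC)), that is by 1.41 to 1.15. Baseline-adjusted z would then be about 2.86 × 1.15 = 3.3 to 3.71 × 1.41 = 5.2, and at the top of that range the method is mostly usable. This stands as a limit on the size of the problem. The article states no baseline adjustment, and the plan should not depend on a favourable result.

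**A reader might infer that the interval would produce false claims of cost-effectiveness.** The simulations show the opposite: over-coverage and little information. Nor does the article make this interval the only basis for judgement, since sensitivity analyses are also planned.

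**A reader might infer that individuals will be resampled in disregard of the couple allocation.** The article does not say so; it leaves the resampling unit open. Keeping couples together is a specification for the replacement and no error in the plan. Likewise, that a condensed article omits a cost-effectiveness plane or net benefit is not the finding. The finding is the method it does state.

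**Conclusion.** The point holds in a limited form. The article fixes an SE-based interval for its primary economic outcome, and that SE has no stable target when the QALY difference may plausibly lie about 2 to 4 standard errors from zero. The consequences are a seed-dependent interval that is usually far too wide, coverage of about 98–100% against 95%, and no separation of dominant from dominated results.

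The size rests on assumptions the article does not supply: that utility shows about f = 0.082, ρ = 0.5, 120 units per arm, and the utility and cost SDs. The AUD widths are illustrations and not a forecast for this trial. With a QALY difference about 5 or more standard errors from zero, the problem largely disappears. The primary clinical outcomes are untouched. The change should be made, but it concerns the economic evaluation only.

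**What to change.** Replace the sentence on bootstrapped standard errors with the following:

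- Bootstrap cost and QALY pairs jointly within arm, keeping both members of a couple together because the couple is the randomised unit.
- Report incremental cost and incremental QALYs, each with a percentile interval.
- Report incremental net monetary benefit with a 95% CI over a stated willingness-to-pay range, or an acceptability curve. Net benefit is linear in the two differences, so its bootstrap SE is finite; its Monte Carlo error is about 1/√(2B), roughly 2% at B = 1,000.
- Give the ICER as a point estimate. If an interval is wanted, use Fieller limits, and accept that they may be unbounded when the QALY difference is not clearly different from zero.

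The cost is a revised sentence and a few lines of code. The data and the bootstrap are the same, and nothing more is asked of participants.

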### Ethical Approval

This trial received ethical approval from the Human Research Ethics Committees of Queensland University of Technology (No. 1400000687) and the Mater Health Services (No. HREC/14/MHS/166). The trial will be implemented in compliance with this protocol and the Australian National Statement on Ethical Conduct in Human Research [59].

## Results

Participant recruitment commenced March, 2015 and continued until October, 2015. Follow-up data collection has commenced and will be completed May, 2016 with results expected in July, 2016.

## Discussion

Depression and distress have substantial impacts on new parents and their babies, with potential to affect later adjustment, relationships, and child development [11-16]. The economic impacts of such depression are also large [17,18]. The perinatal period is an opportunity to engage expectant parents in well-being-based programs, which is particularly important given that better well-being during this phase is associated with positive postpartum outcomes [38]. Although mothers are often the focus of support and interventions during the perinatal phase, fathers also experience perinatal distress, but have received little research attention or support from services, despite a desire to be involved during the perinatal period [45]. Internet interventions offer a flexible, accessible, cost-effective solution for enhancing perinatal well-being in mothers and fathers.

The current research addresses several issues. This project has developed an innovative program with a unique combination of modules, based on several related programs designed by the authors. *Baby Steps* screens for distress and depression, provides childcare resources and interactive tools, and addresses emotional and physical well-being of both fathers and mothers. Key foci are self-selected childcare issues and maintaining pleasurable physical and social activity. Personal tailoring, after-hours availability, rural accessibility, and low cost per user allow the platform to be easily disseminated to large numbers of people across Australia. This study conducts the first perinatal trial to differentiate component effects from a combined intervention of this type, examining distress, functioning, and childcare confidence, and is the first to compare cost-effectiveness of such interventions. As such, this project helps to facilitate the translation of research into policy and practice at state and national levels. *Baby Steps* is one of few trials that focuses on well-being and prevention rather than established depression (thereby having wide applicability), and is also one of the few trials to focus on the well-being of new fathers.

This project has the potential to influence standard services to support parents, thereby increasing their effectiveness, with minimal increases in cost. *Baby Steps* offers a strategy to engage and support fathers, improving their own outcomes as well as their support of mothers, and potentially preventing losses in work time and productivity associated with depression. In concert with other strategies to address the causes of depression and anxiety, this project assists in promoting the long-term emotional and physical health and well-being of Australian children and their families.

